## Abstract

Engaging in physical movement has a number of mental and physical health benefits, and yet 45% of Australia’s population do not meet the recommended guidelines for physical activity. The current study aims to develop an online habit-based intervention designed to reduce sedentary behavior within the workplace, using environmental cues to instigate simple behavioral changes. Participants in this study will include full time office workers who self-report as having a highly sedentary job and work from either a commercial office, home office, or a mixture of both. Participants will complete a habit-based intervention over a four-week period designed to reduce sedentary behavior by increasing habitual responses to simple physical movement behaviors cued by their environment. Analysis will involve mixed methods ANOVAs to test the efficacy of the intervention. A successful intervention will show a reduction in sedentary behavior as a response to habitual simple physical movement behaviors.

## 1. Introduction

In current industrialized societies, health-risk behaviors, such as high levels of sedentary behavior, have been identified as leading causes of disease-related, preventable deaths [1,2,3,4,5,6]. With the increase in technology and decrease in physically demanding jobs, high levels of sedentary behavior and a general disengagement in physical activity are major global health concerns [7,8,9,10,11,12,13]. A particular subset of the population at risk of these concerns are those working in predominately sedentary jobs, such as office workers. Office workers are at particularly high risk for developing conditions related to poor circulation, posture issues, and vision deterioration resulting from computer usage and prolonged sitting [14,15,16,17,18]. As office workers often spend a large proportion of their day engaging in sedentary behavior at work, the workplace has become an opportunistic environment for targeting health-related behaviors [19,20,21,22].

Social cognition theories, such as the theory of planned behavior (TPB–Ajzen [23]), have been applied widely to understand the determinants of sedentary behavior and physical activity [24,25]. Central to many of these models is the premise that intention, which is assumed to be guided by conscious deliberation, is the most proximal predictor of behavior, where the stronger the intention, the more likely the behavior will be acted on [23,24,26,27,28,29,30]. However, it is well documented that the link between intention and behavior is not perfect and that there remains an intention–behavior gap [31]. This gap between intention and behavior highlights a particular concern for interventionalists who aim to develop programs targeted at promoting health behaviors. As those who volunteer for interventions usually report higher intentions, this pragmatic challenge offers a potential explanation to the general lack of long-term effects of behavior change interventions [32,33]. More recently, literature has looked at incorporating constructs that underpin nonconscious processes, such as habit and implicit attitudes, into models predicting sedentary behavior and physical activity and found these more automatic, nonconscious constructs to be important contributors to behavior [34,35,36,37,38,39].

Habit is defined as a psychological construct that is dependent on associations forming between consistent contextual cues and repeated behaviors [40,41,42]. A key feature of habitual actions is that they require less cognitive processing in comparison to intentional behaviors, making the behavior more accessible to perform [43,44]. Research on habit development suggests that it can take anywhere between 18 to 254 days for a behavior to become habitual, dependent on behavioral complexity [45,46]. Physical activity is considered a complex behavior as it requires numerous choices and conducive environmental factors for the behavior to be performed, rendering it more intentional [46,47,48]. For example, to perform physical activity, choices around clothing, transport, and timing need to be considered, along with favorable environmental factors such as the weather; in comparison to simple behaviors such as taking the stairs rather than an escalator when the opportunity presents itself. By focusing on forming habitual responses to cues within the environment that promote physical movement (i.e., stairs), one can increase the amount of movement performed during the day, thus limiting sedentary behavior without taxing cognitive load [49]. Furthermore, as simple behaviors are more conducive to habit formation, they also require less time to reach habit plateau [46]. This suggests that interventions looking to utilize habit formation towards simple behaviors should highlight the measurement of habit development during the early stages of the intervention [46]. As time constraints are often an influencing factor for attrition in physical activity interventions, this structure offers a unique method to counter this barrier [19,22,50].

Studies looking at developing interventions that are aimed at developing habits around performing physical movement should focus on four key aspects: the target behavior is personally relevant; the target behavior is considered a simple change to implement within pre-existing practices; the target behavior is realistic to action; and the target behavior can be monitored and assessed against behavioral goals [45,51]. Furthermore, when developing interventions, previous literature has looked at implementation techniques, comparing internet-based to in person delivery modes. While there appears to be advantages and disadvantages for each method, an internet-based delivery mode offers potential methods for countering common barriers associated with physical activity interventions, such as time constraints. As these barriers contribute to poor attrition rates within physical activity interventions, online interventions provide flexible delivery modes with the added opportunity to reach wider populations [52,53]. Hamilton, Fraser [49] conducted an online pilot study aiming to develop habits around simple physical activity behaviors (e.g., moving the wastepaper bin further away from the desk to encourage more steps) within the workplace, utilizing features outlined by Gardner et al. (2014, 2020). This study found positive trends for habit development among sedentary office workers over a six-week intervention, providing preliminary support for this model.

The current study aims to develop an online habit-based intervention designed to reduce sedentary behavior within the workplace, using environmental cues to instigate simple behavioral changes. Four hypotheses are preregistered for the current study. Based on previous research, the primary objective is to test the effectiveness of the intervention on limiting occupational sedentary behavior and increasing occupational physical movement habits within the workplace. It is hypothesized that reported occupational sedentary behavior will have a decrease (H1) and reported occupational physical movement will have an increase (H2) across baseline (T1) and follow up points two weeks post baseline (T2) and four weeks post baseline (T3) in comparison to those in the control group. It is further expected that occupational physical movement habit will have an increase (H3) and occupational sedentary behavior habit will have a decrease (H4) across baseline (T1) and follow up points two weeks post baseline (T2) and four weeks post baseline (T3).

## 2. Experimental Design

The study is a randomized control trial, designed to reduce occupational sedentary behavior by forming habits towards physical movement within the workplace environment using an online intervention. The study is guided by the SPIRIT (Standard Protocol Items: Recommendations for Interventional Trials) statement [54] (see Appendix A and Appendix B). Participants are recruited from Australian Universities and the general public via email broadcast and provide informed written consent upon registration of their interest to participate. The intervention will be implemented online using Qualtrics software. After baseline data is collected, participants are randomly assigned to either the (1) control group or (2) intervention group electronically through the randomization function within Qualtrics software. Participants will be blinded to the study condition they are assigned to. Time points involve participants completing online surveys assessing social psychological and behavioral constructs at Time 1 (baseline; T1), Time 2 (two weeks postbaseline; T2), and Time 3 (four weeks post baseline; T3), see Appendix C. The intervention protocol is documented and registered on Open Sciences Framework (OSF) and will be updated upon any deviations (see Supplementary Materials). Full ethical approval was granted by the Griffith University Human Research Ethics Committee on 11 June 2020 and last updated on the 8 July 2022 (GU: 2020/401). Any adverse events that occur during the intervention will be documented and reported to the University ethics committee. All data are stored in a secure database accessible to the research team only, in accordance with Griffith University Research Ethics Committee protocol (GU: 2020/401). Data will be checked for errors and deidentified upon collection at T3, with all analyses conducted based on the principle of intention-to-treat [55]. The final data set will be analyzed, with findings written up for publication in peer-reviewed journals and industry reports and for presentation at scientific conferences, and the deidentified data made available on the OSF platform.

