### 3.2. Sample Size

To test intervention effects, there is an intended recruitment of 226 participants. Based on previous research in this field and ongoing research within this population group [56], it is anticipated that there will be approximately a 25% attrition over the four weeks of follow-up for reasons such as changes in job status, vacancy, and failure to complete questionnaires. A total sample of approximately 180 completing participants (90/group) is required to detect a medium effect in habit development towards physical movement. This sample was calculated by a power analysis using WebPower program [57]. Significance level (alpha) was established at 0.05 to avoid a Type 1 error and effect size was determined at f = 0.35. This means that for a 95% chance of detecting a significant intervention effect at a four-week follow-up, approximately 90 participants are needed in each group.

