## 4. Data Analyses

To assess the effect of the intervention on reducing occupational sedentary behavior and increasing occupational physical movement; as well as the interventions effect on increasing occupational physical movement habit and its effects on decreasing occupational sedentary behavior habit, four mixed methods 2 (condition/group) × 3 (time) ANOVA’s will be conducted. To assess the overall effects of the intervention, group (control or intervention) will be used as the between-subjects independent variable; time (baseline/T1, T2 and T3) will be used as the within-subjects independent variable with occupational sedentary behavior, occupational physical movement, occupational physical movement habit, and occupational sedentary behavior habit as the dependent variables. Each ANOVA will use an adjusted alpha level of 0.0125 to protect from inflation of type I error. Results, however, will report on any effects using the conventionally accepted significance cut-off level of 0.05 as well as the pre-specified cut-off level of 0.0125. Where an ANOVA indicates a significant time*group interaction for either of the dependent variables, a simple effects analysis will be conducted.

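### The planned 2 × 3 mixed ANOVAs, in their standard form, leave out participants who miss a survey and so do not by themselves deliver the promised intention-to-treat analysis

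*Protocol article*

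**What the plan says.** Section 2 (Experimental Design) states the analysis principle, "with all analyses conducted based on the principle of intention-to-treat", and places randomisation after the first survey: "After baseline data is collected, participants are randomly assigned to either the (1) control group or (2) intervention group". Anyone who later misses T2 or T3 has therefore already been randomised and has a T1 value.

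Section 4 (Data Analyses) names one method for all four hypotheses, a 2 × 3 mixed ANOVA for each outcome, in which "time (baseline/T1, T2 and T3) will be used as the within-subjects independent variable". Each is tested at 0.0125, and results are also reported against 0.05.

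Section 3.2 (Sample Size) says "there is an intended recruitment of 226 participants", expects "approximately a 25% attrition over the four weeks of follow-up", and counts unreturned questionnaires among the reasons for loss.

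The article names no imputation step or other device for incomplete participants. The SPIRIT checklist in Appendix A marks item 20c (analysis population and missing data) as addressed on a page 9, and item 20b (additional analyses) as not applicable.

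**The concern.** A conventional repeated-measures ANOVA needs a value at every level of the within-subjects factor and deletes any participant who lacks one. Applied as written, Section 4 would analyse those who returned all three surveys, while Section 2 would lead the results to be labelled intention-to-treat. All four hypothesis tests use this method.

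Exclusion after randomisation matters when it is related to response in a way that differs between arms. That is plausible here. Controls receive an information sheet. The intervention arm is also asked for action and coping plans and an encouraging statement, is given a tick sheet, and is encouraged to email it each week. Outcomes are self-reported online, so disengaging from the programme and not returning the survey may be the same event. T2 data from people lost only at T3 would also be discarded.

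**Working it through.** **Inputs from the article:** 226 recruited, 25% attrition, 180 completers wanted (Section 3.2); three time points, level 0.0125 per ANOVA (Section 4). Correlations and drop-out models are not in the article and are assumed below.

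**1. The plan's own figures.** 226 × (1 − 0.25) = 169.5 completers, not 180. Keeping 180 of 226 implies a loss of 46/226 = 20.4%; 180/0.75 = 240; 180 × 1.25 = 225. This is a separate sizing matter that the present point does not need.

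**2. Number left out.** 226 × 0.25 = 56.5, so about 56 to 57 randomised participants are excluded and about 169 to 170 analysed. All 226 have T1 by design.

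**3. Power.** With f = 0.35 and N = 169, the power of the interaction test at 0.0125 is 0.955 with sphericity (ε = 1) and 0.871 with ε = 0.7 (ε is assumed). The main risk is therefore selection, not power.

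**4. Bias, first drop-out model (assumed, no true effect).** Correlations T1–T2, T2–T3 and T1–T3 are 0.6, 0.75 and 0.5. Control drop-out is unrelated to outcome. Intervention drop-out rises by log-odds 0.25, 0.5 or 1.0 per SD of non-improvement from T1 to T2. Each arm has 400,000 participants.

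| Drop-out, control / intervention | Completer bias in T1–T3 change, toward benefit (SD) |
|---|---|
| 20% / 30% | 0.05, 0.11, 0.19 |
| 25% / 25% | 0.05, 0.09, 0.15 |

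Equal attrition rates do not remove the bias. An estimate using T1 and T2 from everyone had a bias of about zero. This is expected, because drop-out was made to depend on data which that estimate uses.

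**5. False-positive rate of a two-group comparison of T1–T3 change.** There are about 85 completers per group (169.5/2). The SD of change is √(2 × (1 − 0.5)) = 1. With shift δ = bias × √(85/2), the two-sided rate is Φ(δ − z) + Φ(−δ − z), where z = 1.96 for 0.05 and 2.498 for 0.0125.

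| Bias (SD) | δ | Rate at 0.05 | Rate at 0.0125 |
|---|---|---|---|
| 0.05 | 0.326 | 6.2% | 1.7% |
| 0.11 | 0.717 | about 11% | 3.8% |
| 0.15 | 0.978 | 16.5% | 6.5% |

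The most extreme scenario (0.19 SD, δ = 1.239) would give about 24% and 10%.

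**6. Second drop-out model (assumed, no true effect), testing group-by-time itself.** 226 are randomised and 25% lost before T3, with intervention drop-out depending on the T2 score. Correlations are either all 0.6 or decay as 0.7 and 0.49; there are 4,000 simulated trials for each. The completer group-by-time test (multivariate form) rejected in about 9% of trials at 0.05 and 3% at 0.0125. The bias was 0.07 to 0.09 SD in the T1–T2 change and about zero in the T1–T3 change. Estimates from all observed data were unbiased.

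**The case against.** No sentence in the article says that incomplete cases are dropped. Imputing before the ANOVA would satisfy Sections 2 and 4 together, an analysis plan that is not shown could provide for it, and checklist item 20c is marked as addressed. This stands in part: the conflict comes from how the named method ordinarily works, not from an explicit exclusion rule. It does not dispose of the point. The article fixes the method, that method needs something added before it can honour the principle, and a better method is available at little cost.

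Three stronger readings are tempting but unsupported.

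- A reader might infer from Section 3.2, "A total sample of approximately 180 completing participants (90/group) is required", that a completer analysis is intended. That sentence sizes the trial. Allowing for attrition is routine and does not define the analysis set.
- A reader might subtract further losses for people who miss only T2. The 25% already includes unreturned questionnaires, and the article gives no separate figure.
- A reader might conclude that the bias favours the intervention. The simulations assume outcome-dependent drop-out in that arm only. The article does not support that assumption: both arms have the same survey schedule, and the tick sheet, printing and emailing are optional or merely encouraged.

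**Conclusion.** The point holds in a limited form. Taken in its standard form, the Section 4 analysis would leave out about 56 to 57 of 226 randomised participants at the plan's own attrition rate, and so does not by itself deliver the Section 2 commitment. That count rests only on the article's figures and the usual behaviour of a mixed ANOVA.

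The consequence is less certain. Bias arises if drop-out is related to response differently in the two arms, and the article fixes neither its direction nor its size. The simulated values are illustrative and rest on assumed correlations and drop-out models. The upper false-positive figures come from strong drop-out dependence, and the figures at 0.05 overstate the risk at the planned level. The 0.0125 threshold lowers the false-positive rate but does not remove the bias.

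**What to change.** In Section 4, replace each ANOVA with a likelihood-based linear mixed model for T1, T2 and T3, with time, group-by-time and an unstructured covariance. Keep T1 in the outcome vector and constrain the baseline means to be equal across arms. Every randomised participant then enters as randomised, and all observed T2 and T3 values are used. A model limited to people with a post-baseline survey would again exclude those lost before T2.

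Test group-by-time jointly at T2 and T3, keeping the 0.0125 level. Report attrition by arm and add one missing-not-at-random sensitivity analysis. Specify all this before outcome data are examined.

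The cost is revised wording, a different routine in standard software and slightly more analysis work; no new data are needed. The model relies on data being missing at random, and people lost before T2 contribute only their T1 value, which is why the sensitivity analysis is needed. If the ANOVAs are retained, stating an imputation step before them would at least reconcile the two sections.

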## 3. Procedure

### 3.1. Recruitment Procedures and Inclusion/Exclusion Criteria

Participants are recruited via the Griffith University email broadcast, University networks, and through social media advertisement. Participants are included if they are aged 18 years or older; self-describe as having a highly sedentary job (i.e., sit for at least 75% of the working day); and work full-time from either a commercial office, home office, or a combination of the two. Participants are excluded if they self-describe as not wanting to limit their sedentary behavior at work.

### 3.2. Sample Size

To test intervention effects, there is an intended recruitment of 226 participants. Based on previous research in this field and ongoing research within this population group [56], it is anticipated that there will be approximately a 25% attrition over the four weeks of follow-up for reasons such as changes in job status, vacancy, and failure to complete questionnaires. A total sample of approximately 180 completing participants (90/group) is required to detect a medium effect in habit development towards physical movement. This sample was calculated by a power analysis using WebPower program [57]. Significance level (alpha) was established at 0.05 to avoid a Type 1 error and effect size was determined at f = 0.35. This means that for a 95% chance of detecting a significant intervention effect at a four-week follow-up, approximately 90 participants are needed in each group.

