## Appendix B. SPIRIT World Health Organization Trial Registration Data Set

**Data category**	**Information ^32^**
Primary registry and trial identifying number	OSF.IO 10.17605/OSF.IO/JASTP
Date of registration in primary registry	6 June 2022
Secondary identifying numbers	N/A
Source(s) of monetary or material support	School of Applied Psychology, Griffith University
Primary sponsor	School of Applied Psychology, Griffith University
Secondary sponsor(s)	Menzies Health Institute Queensland, Griffith University
Contact for public queries	[name] Candidate. [contact]
Contact for scientific queries	[name] Candidate, School of Applied Psychology, Griffith University
Public title	Workplace Physical Movement Program
Scientific title	Physical Movement Habit Formation within Office Workers: Protocol Paper
Countries of recruitment	Australia
Health condition(s) or problem(s) studied	Sedentary behaviour
Intervention(s)	Intervention: habit program; Control: education
Key inclusion and exclusion criteria	Ages eligible for study: ≥18 years. Full time office workers, work from either a commercial office, from home or a mixture of both.
Study type	Interventional allocation: randomized; Intervention model: parallel assignment; Masking: blind (subject); Primary purpose: behaviour change
Date of first enrolment	July 2022
Target sample size	250
Recruitment status	Recruiting
Primary outcome(s)	Developing habits towards simple physical movement behaviours within the workplace
Key secondary outcomes	Reduction in sedentary behaviour

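### Recruiting 226 does not leave the required 180 completers at the stated 25% attrition, and Appendix B gives a different target of 250

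*Protocol article*

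**What the plan says.** Section 3.2 (Sample Size) gives three linked figures in one paragraph.

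- Recruitment: "there is an intended recruitment of 226 participants".
- Attrition: "it is anticipated that there will be approximately a 25% attrition over the four weeks of follow-up".
- Completers: "A total sample of approximately 180 completing participants (90/group) is required to detect a medium effect in habit development towards physical movement".

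The power statement rests on the completer number: "for a 95% chance of detecting a significant intervention effect at a four-week follow-up, approximately 90 participants are needed in each group". The other inputs are alpha ("Significance level (alpha) was established at 0.05 to avoid a Type 1 error") and effect size ("effect size was determined at f = 0.35").

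Appendix B, the WHO registration data set, has a different recruitment figure: "Target sample size 250". It also shows the trial as recruiting. The article does not explain why the two targets differ.

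**The concern.** A recruitment target is the completer requirement divided by the proportion expected to stay. The 226 looks too low for 180 completers at 25% loss, and close to what results when the loss is added on as a percentage. If so, the trial on its own assumptions would finish below the number to which it ties its 95% power.

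The second figure, 250, adds a practical difficulty. The team and later readers have two benchmarks for complete recruitment, about 10% apart, and the same article could be cited for stopping at either.

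**Working it through.** **Inputs.** From Section 3.2: 226 recruited, attrition d = 0.25, 180 completers (90 per group), alpha 0.05, power 95%, f = 0.35. From Appendix B: 250. From Section 4 (Data Analyses), for context: "Each ANOVA will use an adjusted alpha level of 0.0125 to protect from inflation of type I error".

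**Step 1: reproduce 226.**
- Correct inflation, N/(1 - d): 180/0.75 = 240, or 120 per group. This does not give 226.
- Adding the percentage, N x (1 + d): 180 x 1.25 = 225. Done per arm, 90 x 1.25 = 112.5, rounded up to 113, and 2 x 113 = 226 exactly.

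Of the two forms, only the second reproduces the stated number. The article shows no inflation formula, so this is the likely cause and not an established one.

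**Step 2: what each target yields.**

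| Recruited | Completers at 25% attrition | Against 180 | Attrition at which 180 remain |
|---|---|---|---|
| 226 | 226 x 0.75 = 169.5 (about 85 per group) | 10.5 short (5.8%) | 1 - 180/226 = 20.4% |
| 240 | 240 x 0.75 = 180 | met | 25% |
| 250 | 250 x 0.75 = 187.5 | 7.5 over | 1 - 180/250 = 28% |

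**Step 3: effect on power.** The article does not say which ANOVA effect or what sphericity was entered, so I show a range. Power is from the noncentral F with lambda = f² x N x epsilon. Degrees of freedom are 1 and N - 2 for the group effect, and 2 x epsilon and 2(N - 2) x epsilon for the group-by-time interaction over three time points.

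*Anchor A: take 95% at 180 completers and alpha 0.05 as given, with epsilon = 1.* Solving backwards gives f = 0.270 (group) or 0.294 (interaction). Neither is the stated 0.35.

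| Completers | alpha 0.05, group / interaction | alpha 0.0125, group / interaction |
|---|---|---|
| 180 | 95.0% / 95.0% | 86.3% / 86.7% |
| 169.5 | 93.8% / 93.7% | 83.8% / 84.0% |

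The shortfall costs 1.2 to 1.3 points at 0.05 and 2.5 to 2.6 points at 0.0125.

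*Anchor B: take f = 0.35 as given.*

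| Effect, epsilon | alpha 0.05: 180 / 169.5 | alpha 0.0125: 180 / 169.5 |
|---|---|---|
| Group, 1 | 99.7% / 99.5% | 98.5% / 97.8% |
| Interaction, 1 | 99.1% / 98.7% | 96.7% / 95.6% |
| Interaction, 0.7 | 96.4% / 95.4% | 89.5% / 87.2% |
| Interaction, 0.5 | 91.0% / 89.3% | 78.6% / 75.6% |

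With sphericity (epsilon = 1), 169.5 completers still exceed 95% at either alpha. With lower epsilon the level of power falls, but the difference between 180 and 169.5 completers stays at about 1 to 3 points.

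**The case against.** The strongest defence is that every input is hedged: the attrition, the 180 and the 90 per group are all given as approximate, and a 6% shortfall is small against that imprecision. This bears on severity, but it does not rescue 226. Attrition would have to be about 20%, not about 25%, and the hedging does nothing for 226 against 250.

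It could also be said that an intention-to-treat analysis (Section 2) keeps everyone in. But Section 3.2 states its own requirement in completers, so the target has to be judged on completers.

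Two stronger readings are tempting and go too far.

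- A reader might infer that the slip takes power from 95% to about 84%. On anchor A that figure is mostly the effect of testing at 0.0125 when the sample size was set at 0.05. With the full 180 completers, power at 0.0125 is already only 86% to 87%. That mismatch is a separate matter, and recruiting 240 would not remove it. Anchor A also departs from the stated f; at f = 0.35 with sphericity, power stays above 95%.
- A reader might infer that the end of recruitment is undefined. The article gives two conflicting planning numbers, which is an inconsistency to reconcile. The larger one already covers the requirement.

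**Conclusion.** The point holds as an error in the stated sample size. By the document's own figures, 226 at 25% attrition gives about 170 completers instead of 180, and 240 would be needed. Appendix B contradicts Section 3.2 with 250. This part rests on arithmetic alone.

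The consequence is modest. The expected shortfall is 10 to 11 completers, worth about 1 to 3 points of power across the assumptions shown. The article does not support a claim that the error by itself leaves the trial underpowered, because the tested effect and the sphericity are not stated. No test, outcome or design feature changes, and no bias follows. It should be fixed because it is wrong as written, but it does not threaten the trial's conclusions.

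**What to change.** State one recruitment target in both Section 3.2 and Appendix B, and show the inflation as N/(1 - 0.25). Either route is sound.

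- Keep 226, restate the expected completers as about 170 (85 per group), give the power that goes with that number, and change Appendix B to match.
- Align Section 3.2 with the 250 already in Appendix B, which gives about 187 completers at 25% attrition. The minimum for 180 is 240.

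Whichever is chosen, name the ANOVA effect and the sphericity value behind the power figure so that it can be reproduced. The cost is a correction of numbers and wording in two places, with no participants beyond the 250 already listed. As Appendix B shows recruitment under way, it should be settled before recruitment closes and recorded on the OSF registration, where the article says deviations will be posted.

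### The printed inputs (f = 0.35, alpha 0.05, 95% power) give about 109 or 128 completers, not 180, and f = 0.35 is called medium without a benchmark

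*Protocol article*

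**What the plan says.** Section 3.2 (Sample Size) prints the inputs, the result and an interpretation.

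- Result and label: "A total sample of approximately 180 completing participants (90/group) is required to detect a medium effect in habit development towards physical movement".
- Alpha: "Significance level (alpha) was established at 0.05 to avoid a Type 1 error".
- Effect size: "effect size was determined at f = 0.35".
- Power: "for a 95% chance of detecting a significant intervention effect at a four-week follow-up, approximately 90 participants are needed in each group".
- Source: "This sample was calculated by a power analysis using WebPower program". The module, the term tested and any nonsphericity value are not given.

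Section 4 (Data Analyses) sets the design: "group (control or intervention) will be used as the between-subjects independent variable; time (baseline/T1, T2 and T3") is the within-subjects factor. Four such ANOVAs are planned, one per outcome, each at an adjusted alpha of 0.0125. A significant time-by-group interaction leads to simple effects analyses.

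**The concern.** A reader can recompute a sample size when effect size, alpha, power and design are all printed. Here the recomputed figure is far from the printed one, and the alpha is not the one used for testing.

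The verbal label adds a second problem. Someone who reads only the sentence with the word medium will take it that the trial has a 5% chance of missing a medium effect on physical movement habit, one of its primary outcomes. If medium has its usual meaning, that chance is larger, and a null result could be read as stronger evidence of no effect than it is.

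**Working it through.** **Inputs.** From section 3.2: f = 0.35, alpha 0.05, power 95%, 180 completers split 1:1. From section 4: 2 groups, 3 time points, alpha 0.0125 per ANOVA. Assumed: an F test, and the usual benchmarks for f (0.10 small, 0.25 medium, 0.40 large). The article defines none.

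**Formulas.** Power is the upper tail of a noncentral F distribution beyond the central F critical value.

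- Group effect: noncentrality f²N, df 1 and N - 2.
- Group-by-time interaction: noncentrality f²Nε, df 2ε and 2(N - 2)ε, where ε is the nonsphericity value (1 = no correction, 0.5 = the minimum for three measurements).

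**Step 1: reproduce 180.** f² = 0.1225, ε = 1, alpha 0.05.

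- Group effect, N = 109: noncentrality 0.1225 x 109 = 13.35, df 1 and 107, critical F 3.93, power 95.2%. With N = 108 power is just under 95%.
- Interaction, N = 128: noncentrality 0.1225 x 128 = 15.68, df 2 and 252, critical F 3.03, power 95.1%.
- Cross-check for one two-group comparison, where d = 2f = 0.70: 2 x (1.960 + 1.645)² / 0.70² = 53.04, so 54 per group, 108 in total.

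The printed 180 is 65% above 109 (180/109 = 1.65) and 41% above 128 (180/128 = 1.41).

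**Step 2: look for settings that return 180.**

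| Variant (f = 0.35 and 95% power unless stated) | N |
|---|---|
| Alpha 0.0125, group effect / interaction | 144 / 166 |
| One-way or factorial ANOVA variants, alpha 0.05 | 109 to 168 |
| Repeated-measures form with within-person correlation 0 to 0.9 | at most 101 |
| Interaction, alpha 0.05, ε = 0.65 / 0.63 / 0.60 | 176 / 180 / 187 |
| Interaction, alpha 0.0125, ε = 0.9 | 180 |
| Interaction, one-sided 0.05 (run as alpha 0.10), ε = 0.5 | 179 |
| Group effect, f = 0.25, one-sided 0.05 | 175 |

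Every route to about 180 adds an unprinted input or changes a printed one.

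**Step 3: power of 180 completers (ε = 1).**

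| f | Alpha | Group effect | Interaction |
|---|---|---|---|
| 0.35 | 0.05 | 99.7% | 99.1% |
| 0.35 | 0.0125 | 98.5% | 96.7% |
| 0.25 | 0.05 | 91.6% | 85.8% |
| 0.25 | 0.0125 | 79.6% | 70.4% |

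For f = 0.25, 95% power at alpha 0.05 would need 210 (group effect) or 249 (interaction).

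**Step 4: the label.** 0.40 - 0.35 = 0.05 and 0.35 - 0.25 = 0.10, so on the assumed benchmarks 0.35 lies nearer large.

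**Step 5: what 180 detects with 95% power (ε = 1).** For the interaction, f = 0.29 at alpha 0.05 and 0.335 (about 0.34) at 0.0125. For the group effect, 0.27 and 0.31.

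**The case against.** **The error is on the safe side.** A reader might infer that the trial is underpowered or that its stated sensitivity is simply wrong. The document does not support that. Its numerical target is f = 0.35, and without a nonsphericity correction 180 completers exceed 95% power for it at both alpha levels. Even 169.5 completers (226 x 0.75, the printed attrition applied to the recruitment target) give 97.8% and 95.6% at 0.0125. Sensitivity is overstated only for someone who reads medium as f = 0.25, and that benchmark is a convention from outside the article. This objection stands and limits the point.

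**A setting may have been left out.** A reader might also infer that N, power, f and label cannot be reconciled at all. For N, power and f that is too strong: ε near 0.63 returns 180, and a condensed article may omit such a setting. Nor can this route be ruled out because the text speaks of an effect at four weeks. That phrase may describe only the length of follow-up, and section 4 plans no stand-alone comparison at T3. But nothing shows that 0.63 was used. If it was, the safety margin goes at the tested alpha: for f = 0.35 at 0.0125, the interaction needs 231 completers at ε = 0.65 and 246 at ε = 0.60.

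**f = 0.35 is not generally 0.70 SD here.** The conversion d = 2f holds for two groups compared once. For the interaction, assume a group difference growing linearly (0, d/2, d) and equal correlations ρ. The squared deviations of that difference from its mean sum to d²/2, so f² = d² / (8(1 - ρ)) and d = f√(8(1 - ρ)). Then f = 0.35 means d of about 0.83, 0.70 and 0.54 at ρ = 0.3, 0.5 and 0.7. This objection stands too: the label should be judged on the f scale, and a sensitivity in SD units needs an assumed correlation.

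**Conclusion.** The point holds as one about a sample-size statement that is wrong as printed. The printed inputs require about 109 or 128 completers, not 180, and the alpha behind them is not the 0.0125 at which the ANOVAs are tested. At f = 0.35 with ε = 1 the mismatch costs no power.

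The sentence promising detection of a medium effect with 95% power is not supported if medium means f = 0.25. Power is then 86-92% at 0.05 and 70-80% at 0.0125, so the chance of missing such an effect at the tested level is about 20-30% rather than 5%. The lower power figure in each pair belongs to the interaction, the term that triggers the follow-up tests.

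This rests on the noncentral F model above, 180 completers in equal groups, no nonsphericity correction, and the conventional benchmarks. It does not show that the recruitment target is too small for the effect the trial names.

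**What to change.** Keep N. Re-run the calculation for the group-by-time interaction at alpha 0.0125, and print the WebPower module, the term tested and the nonsphericity value used. Replace the word medium with the f that 180 completers detect with 95% power: without a nonsphericity correction, about 0.34 for the interaction at 0.0125 (0.29 at 0.05). With a correction the detectable f is larger and should be recomputed.

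A sensitivity quoted for a single T3 comparison would not do, because section 4 does not make that the deciding test.

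The cost is one rewritten paragraph and the loss of the claim of 95% power for a medium effect.
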